## ELIGIBILITY CRITERIA

### Inclusion Criteria

Patients with mCRPC.Patients must have received at least one regimen of chemotherapy for mCRPC.Patients must have received at least one androgen receptor signaling inhibitor.Patients must be eligible by PSMA PET VISION criteria (2). PSMA PET/CT must be performed within 8 wk of planned first cycle of [^177^Lu]Lu-PSMA-617.Patients must have sufficient bone marrow capacity as defined by a white blood cell count of at least 2,500/μL, platelet count of at least 100,000/μL, hemoglobin of at least 9.0 g/dL, and absolute neutrophil count of at least 1,500/μL.Patients must have an ECOG performance status of 0 to 2.Patients must be adults at least 18 y of age.Patients must have the ability to understand and sign an approved informed consent form and comply with all protocol requirements.

### Exclusion Criteria

Prior [^177^Lu]Lu-PSMA-617 therapy.Less than 6 wk between last myelosuppressive therapy (including docetaxel, cabazitaxel, ^89^Sr, ^153^Sm, ^186^Re, ^188^Re, ^223^Ra, hemibody irradiation) and first cycle of [^177^Lu]Lu-PSMA-617 therapy.Estimated glomerular filtration rate of less than 50 mL/min.Urinary tract obstruction or marked hydronephrosis.

## INVESTIGATIONAL PLAN

A schedule of assessments is provided in the full study protocol in the supplemental materials. The study procedures are described in section 6 of the study protocol.

## TREATMENT DRUG

[^177^Lu]Lu-PSMA-617 will be supplied by Novartis. For further details regarding packaging, storage, administration, accountability, and product retention please see section 4.2 of the study protocol in the supplemental materials.

## INVESTIGATIONAL ARM TIMELINE

In the investigational arm (*n* = 45), patients will receive intravenous injection of 7.4 GBq (±10%) of [^177^Lu]Lu-PSMA-617 once every 6 wk (±1 wk) for a maximum of 12 cycles until disease progression (except for progression during treatment holiday periods which will lead to treatment continuation) or unacceptable toxicity.

Evaluation of treatment response is performed using posttreatment SPECT/CT and PSA at every cycle. Radiographic response assessment at every cycle uses posttreatment SPECT/CT of cycle 1 as the baseline. If a patient experiences either a PSA decline of 90% or more or a PSA level of less than 1.0 and CR, or a PSA decline of 90% or more or a PSA level of less than 1.0 and PR plus tumor uptake below liver uptake on either SPECT/CT or PET/CT, the subsequent cycle will be postponed until disease progression. The investigational arm is illustrated in Figure 2.

**FIGURE 2. fig2:**
[figure not shown]
Investigational arm. Patients in investigational arm are treated with up to 12 cycles including potential “treatment holidays” depending on response. Response assessment is based on SPECT/CT and PSA at each cycle during treatment periods. C = treatment cycle; RR = relative response/response rate.

During the treatment holiday period and after the 12th cycle, the disease control and progression will be assessed every 12 wk by PSA and PSMA PET/CT using RECIP (13). According to RECIP, a CR is defined as the absence of any PSMA-ligand uptake on interim PET/CT (RECIP-CR), a PR is defined as a decline of at least 30% in PSMA volume (PSMA-VOL) and no appearance of new lesions, progressive disease (PD) is defined as an increase of at least 20% in PSMA-VOL and appearance of new lesions (RECIP-PD), and SD (RECIP-SD) is defined as any condition but RECIP-PR or RECIP-PD.

The treatment holiday period is illustrated in Figure 3. Once [^177^Lu]Lu-PSMA-617 treatment is restarted after a treatment holiday, evaluation of treatment response is performed using posttreatment SPECT/CT and PSA at each cycle. Radiographic response assessment at each cycle uses posttreatment SPECT/CT of cycle 1 as the baseline.

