i.Marked escalation in cancer-related pain that is assessed by the investigator to indicate the need for other cytotoxic systemic therapy for prostate cancer.ii.Immediate need for initiation of new anticancer treatment, surgical or radiologic intervention for complications due to tumor progression even in the absence of radiologic progression.iii.Marked deterioration in Eastern Cooperative Oncology Group (ECOG) performance status to grade 3 or greater or in the opinion of the investigator ECOG deterioration indicates clinical progression.iv.In the opinion of the investigator, it is in the best interest of the patient to discontinue treatment due to clinical progression.To determine disease control rate defined as the proportion of patients achieving radiographic stable disease (SD), partial response (PR), or CR. CR is defined as absence of a PSMA-avid tumor on either imaging modality. On SPECT/CT, PR is defined as a greater than 30% reduction in visual tumor volume at all sites of involved disease compared with baseline cycle 1, no new sites of PSMA-avid tumor, and no new sites of PSMA-negative tumor on CT; and SD is defined as no change greater than 30% in visual tumor volume compared with baseline cycle 1, no new sites of PSMA-avid tumor, and no new sites of PSMA-negative tumor on CT. Respective response groups on PSMA PET/CT are defined by RECIP (13).To determine disease control rate by combined radiographic plus PSA response with response defined as PSA decline of 50% or more or radiographic PR/CR as defined above.To determine changes in of HRQoL using the following:
a.The Brief Pain Inventory–Short Form. Pain response defined by improvement from baseline (all patients with ≥4/10) of at least 2-point absolute improvement without an overall increase in opiate use.b.Changes in performance status (ECOG).c.The FACT-RNT questionnaire (14).

**TABLE 1. tbl1:** SPECT/CT Response Assessment Criteria

SPECT/CT	CR	PR	SD	PD
Response assessment criteria adopted from Emmett et al. (10)	Absence of any PSMA uptake, no new sites of PSMA-negative tumor	>30% decrease in PSMA-VOL, no new sites of PSMA-positive or PSMA-negative tumor	No change >30% in PSMA-VOL, no new sites of PSMA-positive or PSMA-negative tumor	>30% increase in PSMA-VOL ± new sites of PSMA-positive or PSMA-negative tumor, or new sites of PSMA-negative tumor on CT

SPECT/CT Response Assessment Criteria.

**TABLE 2. tbl2:** PET/CT Response Assessment Criteria

PET/CT	CR	PR	SD	PD

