Response assessment criteria adopted from Gafita et al. (RECIP) (13)	Absence of any PSMA uptake, no new sites of PSMA-negative tumor	≥30% decrease in PSMA-VOL without new sites of PSMA-positive or PSMA-negative tumor	<30% decrease in PSMA-VOL ± new sites of PSMA-positive or PSMA-negative tumor *or* <20% increase in PSMA-VOL ± new sites of PSMA-positive or PSMA-negative tumor *or* PR with new lesions *or* PD without new lesions	≥20% increase in PSMA-VOL with new sites of PSMA-positive or PSMA-negative tumor

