## STUDY DURATION

Patients may be treated for up to 12 cycles (investigational arm) or 6 cycles (control arm) of [^177^Lu]Lu-PSMA-617 therapy until progressive disease (except for progression during treatment holiday periods in the investigational arm which will lead to treatment continuation), withdrawal of consent, the occurrence of unacceptable toxicity, or a determination by the investigator if the patient is not clinically benefiting.

The duration of subject participation will be from the time of signing informed consent through the 24-mo postinjection visit. The planned duration for the whole study is 48 mo. The study enrollment started in August 2024. Trial completion date is anticipated for December 2028.

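### After a holiday restart, a lesion absent at cycle 1 but visible on SPECT/CT rules out PR and SD, so the progression that required the restart can stop dosing one cycle later

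*Protocol article*

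**What the plan says.** All references are to the protocol article.

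- **Baseline after restart.** Investigational Arm Timeline, in the text on restarting after a holiday: "Radiographic response assessment at each cycle uses posttreatment SPECT/CT of cycle 1 as the baseline". The same baseline applies to cycles before a holiday.
- **Imaging progression on holiday.** The same section: "progressive disease (PD) is defined as an increase of at least 20% in PSMA-VOL and appearance of new lesions (RECIP-PD"). Table 2 specifies the kind of lesion: "≥20% increase in PSMA-VOL with new sites of PSMA-positive or PSMA-negative tumor".
- **SPECT/CT classes (Table 1).** PR: ">30% decrease in PSMA-VOL, no new sites of PSMA-positive or PSMA-negative tumor". SD: "No change >30% in PSMA-VOL, no new sites of PSMA-positive or PSMA-negative tumor". PD: ">30% increase in PSMA-VOL ± new sites of PSMA-positive or PSMA-negative tumor, or new sites of PSMA-negative tumor on CT". CR needs absence of uptake and bars only new PSMA-negative sites.
- **Stopping rule.** Investigational Arm Timeline: dosing runs "until disease progression (except for progression during treatment holiday periods which will lead to treatment continuation"). Study Duration repeats it: "until progressive disease (except for progression during treatment holiday periods in the investigational arm which will lead to treatment continuation").
- **Scan timing.** The post-treatment SPECT/CT is acquired 24 to 72 h after each dose (177Lu-PSMA SPECT/CT Imaging).

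**The concern.** Restarting after holiday progression is central to the flexible schedule. A patient restarted for RECIP-PD has, by definition, at least one new lesion. If that lesion was not there at cycle 1, a scan compared with cycle 1 counts it as new again. The first post-restart scan comes within three days of the dose, which is too soon to expect that dose to have cleared the lesion. The scan also falls on treatment, outside the period that the exemption names.

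Two things are at stake. The progression that required the restart can be read as the progression that stops treatment. And a patient whose tumor shrinks well after the restart can be kept from a further holiday by PR because one site is still called new.

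**Working it through.** The article's only design calculation, 80.3% power, plays no part here. The check applies Table 1 as written.

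**Inputs.** Let r be the SPECT/CT volume divided by the cycle 1 volume. From Table 1, with uptake still present:

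- PR: r < 0.70 and no new site of either kind.
- SD: 0.70 ≤ r ≤ 1.30 and no new site of either kind.
- PD: r > 1.30, or a new PSMA-negative site at any r.

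The prose under Secondary Endpoints puts the PD threshold at 30% or greater. That differs from Table 1 only at exactly +30% and does not matter here.

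**Enumeration**, r = 0.01 to 2.00 in steps of 0.01 (200 values):

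| Sites new versus cycle 1 | PR | SD | PD | No class |
|---|---|---|---|---|
| None | 69 | 61 | 70 | 0 |
| PSMA-positive only | 0 | 0 | 70 (r > 1.30) | 130 (r ≤ 1.30) |
| PSMA-negative | 0 | 0 | 200 | 0 |

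These counts show which classes are reachable. They are not frequencies of patients.

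**Worked cases.** All volumes are assumed: cycle 1 at 500 mL, and holiday entry at PR with 100 mL and uptake below liver. The article does not say which scan RECIP growth and new lesions are measured against during a holiday, so both readings are shown.

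- **A. PET reference is holiday entry; new PSMA-positive lesion absent at cycle 1.** PET at 150 mL: 150/100 = +50% with a new lesion, so RECIP-PD and restart. Post-restart SPECT/CT: 150/500 = −70% with a new site, so no class. Later, at 20 mL: 20/500 = −96% with the site still visible, still no class and no holiday by PR.
- **B. As A, but the new lesion is PSMA-negative.** SPECT/CT at −70% is PD after one restart dose.
- **C. PET reference is the pre-treatment scan; new PSMA-positive lesion.** PET at 600 mL is +20% with a new lesion, so RECIP-PD. SPECT/CT at 600 mL (+20%) has no class; at 655 mL (655/500 = +31%) it is PD.
- **Contrast: as A, but the lesion was present at cycle 1, vanished and came back.** It is new on PET against holiday entry but not new against cycle 1. SPECT/CT at −70% is PR.

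**The same cases with the first post-restart scan as reference.** In A, 20/150 = −87% with no site new against that scan, so the PR volume and new-site conditions are met. In A and B, PD by volume needs more than 1.30 × 150 = 195 mL, or a new PSMA-negative site. In C at 655 mL, PD by volume needs more than 1.30 × 655 = 851.5 mL.

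**The case against.** Much of the case on the other side stands.

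- **Not every RECIP-PD restart is affected.** A reader might infer that any such patient can afterwards only be PD or unclassifiable. The documents do not support that. The RECIP reference scan is unstated, so a cycle 1 lesion that vanished and recurred leaves PR and SD open. A small PET lesion may not show on SPECT/CT. CR is formally available once all uptake is gone, provided there is no new PSMA-negative site. PSA is also followed on holiday, so a restart need not come from RECIP-PD.
- **No class does not mean no dosing.** The default is a dose every 6 wk until progression or unacceptable toxicity, and an unclassified scan is not progression. Withholding a holiday while a new avid lesion persists is also clinically defensible.
- **PSA.** A reader might extend the point to PSA, because its progression is measured from the nadir. That text defines the date of a PFS event. Nothing makes it a stopping rule to be tested again at each visit after restart.
- **Stopping may be right.** Ending a PSMA-targeted drug for PSMA-negative disease can be defended on its merits.

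The strongest objection is that a sensible investigator would treat the first post-restart scan as showing the same, already exempted progression. That is a fair reading of intent, but the text limits the exemption to the holiday period. If the exemption did carry over, patients in the PD cases would have no working imaging stop rule: with a PSMA-negative site, every volume is PD against cycle 1, so further growth could not be told from the exempted progression.

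Sections 6.8 and 6.9 of the full protocol, which are not shown, may settle this. The sentence in the article would then need to match them.

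**Conclusion.** The point holds in a limited form. Where a holiday ends in RECIP-PD, and the new lesion was absent at cycle 1 and is visible on SPECT/CT, PR and SD are unavailable while the site remains visible. A PSMA-negative site gives PD at any volume, and volume more than 30% above cycle 1 gives PD with either kind of site. The exemption does not literally cover that scan, so dosing can stop after one restart dose. A PSMA-positive site at or below +30% gives no class: dosing continues, but a further holiday by PR is closed.

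The effect is on dosing in the investigational arm, and the article gives no basis for the number affected. A reader might also infer damage to the endpoints or to power. That is not shown. The primary endpoint does not use these classes. For a patient restarted after RECIP-PD, the first progression for PFS has already occurred, and holiday entry already required CR or PR. This is a low-cost improvement to consider, not a flaw in the primary comparison.

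**What to change.** 1. In the Investigational Arm Timeline, state that for dosing decisions after a restart the imaging reference is the first post-restart SPECT/CT. Progression already present on that scan does not count as new PD; later growth or new sites against it do.
2. Keep cycle 1 as the baseline for PFS and the disease control endpoints.
3. In Table 1, assign a class to new PSMA-positive sites without a volume increase above 30%.
4. If section 6.9 of the full protocol already re-baselines, correct the article's sentence to agree.

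**Cost.** A short text amendment and one table entry. SPECT/CT is already planned at every cycle, so there are no added scans or visits and no change to the sample size. The drawback is that a patient with a PSMA-negative lesion present at restart may receive further doses. The provision under Study Duration that lets the investigator stop a patient who is not benefiting limits this. Enrollment began in August 2024, so the amendment should be made promptly, ideally before the first restarts.

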**FIGURE 3. fig3:**
[figure not shown]
Treatment holidays. Patients with exceptional response in investigational are put on “treatment holidays.” Response assessment during treatment holiday periods is based on PSMA PET/CT and PSA every 12 wk. RECIP = response evaluation criteria in PSMA PET/CT; RR = relative response/response rate; VOL = volume.

Safety will be closely monitored following Common Terminology Criteria for Adverse Events with laboratory assessments every 3 wk during the treatment period and during the first 3 mo after the last cycle, and every 3 mo during the remaining follow-up time up to a total of 24 mo. Data will be collected for any adverse events. An interim safety analysis with a stopping rule based on safety outcomes is planned at 50% of enrollment.

Single-time-point SPECT/CT dosimetry protocol (15) at each cycle will be performed to determine the number of cycles that subjects may receive regarding dose-limiting organs. If the calculated kidney biologically effective dose exceeds 39 Gy by dosimetry, the total number of cycles should be adapted and limited to stay under the 39-Gy biologically effective dose limit.

## CONTROL ARM TIMELINE

In the control arm (*n* = 45), patients will receive intravenous injection of 7.4 GBq (±10%) of [^177^Lu]Lu-PSMA-617 once every 6 wk (±1 wk) for a maximum of 6 cycles. Evaluation of treatment response is performed using posttreatment SPECT/CT and PSA every cycle. After termination of [^177^Lu]Lu-PSMA-617 treatment, the disease control and progression will be assessed every 12 wk by PSMA PET/CT and PSA.

## MANAGEMENT OF TOXICITY

Details on toxicity risk reduction and supportive care for [^177^Lu]Lu-PSMA-617 injections, the management of toxicity adverse events, with dosing delays and modification are provided in section 5.3 of the study protocol in the supplemental materials.

## Concomitant Medications

Concomitant first-generation androgen deprivation therapy is allowed. Local external beam radiotherapy, including palliative external radiation, is allowed.

Any other treatments for prostate cancer are not allowed, including switch or initiation of second-generation androgen receptor axis inhibitors (abiraterone, enzalutamide, darolutamide, apalutamide), taxane- or platin-based chemotherapy (washout period of 6 wk before first cycle of [^177^Lu]Lu-PSMA-617 RPT), RPT (including ^89^Sr, ^153^Sm, ^186^Re, ^188^Re, ^223^Ra; washout of 6 wk before first cycle of [^177^Lu]Lu-PSMA-617 RPT), sipuleucel-T, olaparib, rucaparib, and pembrolizumab (washout period of 4 wk before first cycle of [^177^Lu]Lu-PSMA-617 RPT).

Supportive care should be provided as deemed necessary by the treating physician.

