### Secondary Endpoints

The secondary endpoints included the following.
To evaluate the safety of a flexible dosing schedule of [^177^Lu]Lu-PSMA-617 including up to 12 cycles and “treatment holiday” periods by Common Terminology Criteria for Adverse Events guidelines and dosimetry.To determine the overall survival, defined as the time from the date of the first cycle injection of [^177^Lu]Lu-PSMA-617 until death.To determine the PFS defined as the date of the first cycle injection of [^177^Lu]Lu-PSMA-617 to the date of first evidence of progression as defined by either radiographic progression, PSA progression, clinical progression, or death from any cause, whichever occurs first.
a.Radiographic progression is defined as the date of radiographic disease progression on SPECT/CT by visual increase in tumor volume of 30% or greater compared with baseline cycle 1 ± new sites of disease or new sites of PSMA-negative disease progression on CT (10,12) or on PSMA PET/CT as outlined in RECIP or by apparition of new PSMA-negative disease measurable on CT (13). Response assessment criteria using SPECT/CT are summarized in Table 1, and response assessment criteria on PET/CT are summarized in Table 2. See sections 6.8 and 6.9 in the study protocol in the supplemental materials.b.PSA progression is defined as the date when a 25% or greater increase in PSA and an absolute increase of 2 ng/mL or more from the nadir is documented and confirmed by a second consecutive value obtained 3 or more weeks later. Rises in PSA within the first 12 wk will be ignored in the absence of other evidence of disease progression in accordance with the Prostate Cancer Clinical Trials Working Group recommendations. Where no decline from baseline is documented, PSA progression is defined as a 25% increase from the baseline value along with an increase in absolute value of 2 ng/mL or more after 12 wk of treatment.c.Unequivocal clinical progression is defined as follows:

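### The pain-response rule does not guard against permitted palliative radiotherapy, and the PFS definition leaves unclear whether that radiotherapy is a progression event

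*Protocol article*

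**What the plan says.** All references are to the protocol article.

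- **Concomitant Medications** permits radiotherapy: "Local external beam radiotherapy, including palliative external radiation, is allowed". The article states no limit on timing, site or indication. The next paragraph opens with "Any other treatments for prostate cancer are not allowed", which places external beam radiotherapy among the treatments for prostate cancer.
- **Secondary Endpoints, pain response** applies to patients with a baseline score of 4/10 or more and requires "at least 2-point absolute improvement without an overall increase in opiate use". No other co-treatment is mentioned.
- **Secondary Endpoints, PFS** ends at "first evidence of progression as defined by either radiographic progression, PSA progression, clinical progression, or death from any cause, whichever occurs first".
- **Secondary Endpoints, clinical progression item i** reads: "Marked escalation in cancer-related pain that is assessed by the investigator to indicate the need for other cytotoxic systemic therapy for prostate cancer".
- **Secondary Endpoints, clinical progression item ii** reads: "Immediate need for initiation of new anticancer treatment, surgical or radiologic intervention for complications due to tumor progression even in the absence of radiologic progression".
- **Study Duration** lets treatment run until disease progression, among other reasons for ending it, with an exception for progression during a treatment holiday in the investigational arm.
- **Statistics and Sample Size Determination** confirms that study team and patient both know the allocated arm.

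**The concern.** Palliative radiotherapy is given to relieve pain. If pain response is meant to describe the effect of the dosing schedule, relief that follows external radiation should not be credited to that schedule. The authors evidently saw the general problem, because they exclude relief obtained with more opiates. They did not extend the exclusion to a second pain-relieving treatment that the protocol expressly allows.

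Radiotherapy use could also differ by arm. Control patients receive at most 6 cycles; investigational patients may receive up to 12, with possible breaks. The periods in which a painful site has no study drug available therefore differ between the arms, and the people deciding on radiotherapy know the arm. The article does not show which arm would use more, so the direction of any distortion is unknown.

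For PFS the stake is consistency. If one assessment records an irradiation as permitted supportive treatment and another records it as clinical progression, PFS depends on an unblinded label. Because progression also ends study treatment outside holidays, an allowed co-treatment might itself mark the end of study treatment.

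**Working it through.** The article gives no figure on this point to reproduce. The check sets the rules side by side.

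**Pain response.** Take a patient with baseline pain of at least 4/10 who is irradiated at a painful site, whose score then falls by 2 points and whose opiate use does not rise.

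1. Is the irradiation permitted? Yes (Concomitant Medications).
2. Is the baseline condition met? Yes.
3. Is the 2-point condition met? Yes.
4. Is the opiate condition met? Yes.
5. Is there any other condition? None is stated.

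Followed as written, the rule scores a pain response. Had the same relief come with an overall increase in opiates, it would not.

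**PFS.** The status of the procedure depends on how item ii is read:

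| Situation | Item i | Item ii |
|---|---|---|
| Radiotherapy for pain alone | No event, unless the pain indicates a need for cytotoxic systemic therapy | Event only if the painful lesion is taken as a complication of progression, or the radiotherapy as an immediately needed new anticancer treatment |
| Radiotherapy for an urgent tumor complication | Does not apply | Event if radiologic intervention includes radiotherapy, or if radiotherapy counts as new anticancer treatment; no event if the phrase means interventional radiology and a permitted treatment is not counted as new |

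The second row is the most clearly open. Even if radiologic intervention is confined to interventional radiology, the new-treatment route remains, because Concomitant Medications groups radiotherapy with prostate cancer treatments. The first row leans towards no event, but item ii does not settle it.

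**Size.** The article gives neither a rate of palliative radiotherapy nor a rate of pain relief after it. For orientation only, *assume* that 10–20% of patients with baseline pain of 4/10 or more are irradiated, and that 40–60% of those gain 2 points:

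- Share of the pain-response rate within one arm: 0.10 × 0.40 = 0.04 to 0.20 × 0.60 = 0.12, that is 4 to 12 percentage points.
- Difference between arms, with the same relief fraction in both: about 0 if use is equal; (0.20 − 0.10) × 0.60 = 0.06, or 6 points, if one arm sits at each end of the assumed range.

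These are ceilings under the assumed rates. They suppose that no irradiated patient would have responded without radiotherapy and that none increased opiates.

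**Primary endpoint.** The stated 80.3% power concerns survival at 24 months (0.30 against 0.55). Neither pain nor PFS enters it.

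**The case against.** The strongest reply has four parts.

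- **Permission and event status are different things.** A treatment may be allowed while the need for it marks progression. This is right. A reader might infer a contradiction because one irradiation can score as failure on PFS and success on pain. The documents do not support that, since these are separate endpoints and a patient can progress and still have less pain. What remains is that the event status is unclear and that the pain endpoint is confounded.
- **Item i already deals with pain.** It largely does, and so the PFS ambiguity is narrower than it first looks: item ii speaks of immediate need and of complications of progression. It does not remove the ambiguity for urgent complications. Nor would relabelling always create or remove an event, because PFS also ends at PSA or radiographic progression or death; often it would only move the date.
- **The full protocol may hold the handling rule.** It may, and it is not shown. Silence on analysis detail would not be a finding. But the article itself fixes the pain rule, including its opiate condition, and the list of progression events, and the point rests on those stated rules.
- **Between-arm differences are conjecture.** They are possible, not demonstrated. Investigational patients who progress on treatment also stop; further cycles go to those not progressing or resuming after a holiday.

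A reader might also infer that irradiating one lesion could produce a radiographic or PSA response and so trigger a treatment holiday. The documents do not support this. The Secondary Endpoints text requires a SPECT/CT partial response to show more than 30% reduction at all involved sites. The holiday rule ("PR plus tumor uptake below liver uptake on either SPECT/CT or PET/CT, the subsequent cycle will be postponed until disease progression") also needs a PSA decline of 90% or more or a PSA below 1.0. Nothing in the article indicates that local irradiation would achieve this in disease at several sites.

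Nor can an assumed use rate among patients with pain be multiplied into all 45 patients per arm to count affected PFS events: the denominator is wrong, and the label need not decide whether an event occurs.

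**Conclusion.** The point holds in a limited form. As written, the pain-response rule credits relief after permitted radiotherapy to the study schedule. This follows from the rule's single, opiate-only condition, not from any statement that such relief should count. The PFS definition also leaves the status of permitted palliative radiotherapy open, mainly for urgent complications, in a trial where the person applying the label knows the arm.

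Only secondary endpoints are affected. The size cannot be derived from the article; the 4 to 12 points within an arm, and 0 to 6 points between arms, are ceilings on assumed rates. The conclusion rests on the article alone. If the full protocol contains a handling rule, the article's wording should be brought into line with it.

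**What to change.** 1. **Pain response.** Count a patient as a non-responder from the start of radiotherapy to a painful site, in parallel with the existing condition on opiates. Scores taken before that date still count. Confine the rule to scoring this endpoint.
2. **Reporting.** Report radiotherapy use by arm, so that any imbalance is visible.
3. **PFS.** Reconcile clinical progression items i and ii, Concomitant Medications and Study Duration, so that the PFS status of permitted radiotherapy follows one written rule applied identically in both arms. Which way that rule goes is for the trial team to decide.

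The cost is a change of endpoint wording, with no change to the sample size. The pain-response rate will be slightly lower, and some patients who would have responded anyway will be scored as non-responders. Dates and sites of radiotherapy must be available; the article does not say that they are recorded, so this should be confirmed.
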